### Study Aim and Hypotheses

The aim of this RCT is to evaluate in insufficiently active ACS patients, the effect of a fully automated, Web-based tailored nursing intervention (TAVIE en m@rche) on increased steps per day. Our primary hypothesis is that ACS patients in the experimental group receiving TAVIE en m@rche compared with the control group receiving hyperlinks to publicly available websites will demonstrate a greater increase in change in steps per day between randomization and 12 weeks (H1). Secondary hypotheses are a greater increase in change in steps per day between randomization and 5 weeks (H2), and in energy expenditure for walking and moderate to vigorous physical activity between randomization and 5 weeks, and randomization and 12 weeks (H3 to H6).

We are interested in assessing if the change in SDT variables immediately postintervention at 5 weeks will explain the hypothesized increase in steps per day at 12 weeks. Therefore, we will explore the mediating role of the SDT constructs (perceived autonomy support, controlled and autonomous motivations, perceived competence) and barrier self-efficacy on the effect of TAVIE en m@rche on increased steps per day at 12 weeks (H7 to H11 respectively).

We will also explore the effect of TAVIE en m@rche at 12 weeks on improved quality of life (global, emotional, physical, and social), smoking, medication adherence, secondary prevention program attendance, emergency visits, and hospitalizations (H12 to H20). The potential moderating role of sex on the effect of TAVIE en m@rche on steps per day at 12 weeks will also be explored (H21). Finally, we expect no adverse effect, which is represented by an equal level of angina symptom frequency at 12 weeks in both groups (H22).

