### Sample Size Calculation

To detect a difference in change between randomization and 12 weeks of 1500 steps per day (SD 2824) in favor of the experimental group compared with the control group, a total of 148 participants (n=74 participants per group [57 plus 17 for attrition], and n=37 per recruitment center) is needed, given a two-sided 5% significance level, power of 80%, and an expected attrition of 23%. The 1500 steps per day is an approximation of half of the recommended daily minutes of moderate intensity physical activity [47]. The attrition of 23% was reported in a meta-analysis of Web-based interventions, in which the experimental groups had an average intervention duration of 13 weeks [17]. The SD of 2824 steps per day was estimated using data found in an RCT of a counseling intervention in ACS patients in Quebec [48].

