#### Clinical Outcomes

Quality of life is assessed at baseline and 12 weeks by the French version MacNew Heart Disease Health-related Quality of Life Questionnaire for cardiac patients [28]. The 27 items assess, in the previous 2 weeks, global quality of life and its 3 subdimensions: emotional (14 items), physical (13 items), and social (13 items) [56]. Items include reverse scores and overlap across dimensions. The scores for global quality of life and each dimension are the mean of responses that range between 1 (poor quality of life), and 7 (high quality of life). Reported Cronbach alphas were .94, .94, .89, and .90 in global, emotional, physical, and social respectively [57].

Self-reported 7-day point prevalence smoking status, an accepted norm in assessing smoking status outcomes [58], is assessed at baseline and 12 weeks. The following question is used: “Have you smoked a cigarette, even a puff, in the past 7 days?” (p. 4 [59]), answered with “yes” (0), “no” (1), or “never smoked” (2). Point prevalence assessment had a sensitivity of 96.9% and specificity of 93.4% in detecting dichotomous smoking versus nonsmoking status compared with urinary cotinine [60].

Medication adherence is assessed at baseline and 12 weeks by the Self-Reported Morisky Medication Adherence Scale (MMAS-4) [61]. This measure assesses barriers to cardiac medication use in the previous 2 weeks such as forgetting to take them and stopping them because one feels well. The score is the sum of 4 items rated “no” (0) or “yes” (1) such that lower scores indicate better medication adherence. Scores are dichotomized between medium to low (1 to 4) and high (0). The MMAS-4 had a sensitivity and specificity of 81.0% and 44.0% respectively in predicting controlled blood pressure [61].

Secondary prevention program attendance is measured at 12 weeks by self-report rated by “no” (0) or “yes” (1) of at least one visit, since hospitalization, to a secondary prevention program that offers clinical follow-up with a health care professional for general health, medication adherence, healthy diet, smoking cessation, or exercise. No data on baseline attendance are collected because programs may start 4 weeks or later posthospitalization, which falls around the planned time of randomization.

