### Statistical Methods

The Montreal Health Innovations Coordinating Center provided expertise for the statistical methods. Baseline characteristics will be compared using descriptive statistics to identify trends in group imbalances, and the analyses will be consistent with intention-to-treat principles, in which data at a given time point will not be excluded from the analysis [64]. Missing data will be examined and handled according to best practice in that field [65].

For the analyses of single continuous variables (eg, the primary outcome of change in steps per day), repeated measures analysis of covariance models will be used with covariates that include gender, age, diabetes, intermittent claudication, baseline smoking status, depression symptoms, and fatigue. For analyses of multiple continuous variables (eg, the secondary outcomes of change in walking and moderate to vigorous physical activity), repeated measures multivariate analysis of covariance models will be used with the same covariates as the above model. For single dichotomous variables with baseline values (eg, smoking status), sequential logistic regression models will be used. For single dichotomous variables without baseline values (eg, hospitalizations), chi-square models will be used. A mediation analysis will use a sequence of one-way analysis of variance models with Bonferroni adjustments, in which the alpha will be divided by the number of tests performed. Adjusted and unadjusted means or proportions in each group (experimental and control) will be provided along with a 95% confidence interval. No adjustments in *P* values will be made for the hypotheses on secondary and tertiary outcomes because these are aimed at supporting the primary hypothesis on steps per day rather than claiming intervention effect [66].

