Fourth, it is possible that accelerometers are worn by or data from online questionnaires are entered by someone other than the study participant because the outcome data are completed by participants at home. Although we will treat this possibility when examining the outliers, which could reveal some data clearly out of range entered by a different respondent, there are no other provisions made for this limitation.

Fifth, there is a possibility of missing outcome data. Different scenarios for handling missing data will be followed according to best practice in that field [65] by a statistician who is part of an internationally recognized clinical trial reference center (Montreal Health Innovations Coordinating Center). The method of handling missing data will be reported in a future publication of the results.

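### The joint MANCOVA does not decide H3 to H6 one by one, and the repeated-measures model for steps is not tied to the 12-week change on which H1 and the sample size rest

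*Protocol article*

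**What the plan says.** The Study Aim and Hypotheses section of the protocol article states H1 as a greater increase in steps per day from randomization to 12 weeks, and H2 as the same to 5 weeks. It then adds a greater increase "in energy expenditure for walking and moderate to vigorous physical activity between randomization and 5 weeks, and randomization and 12 weeks (H3 to H6"). That is two variables over two intervals, so four hypotheses, each with a direction.

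The Sample Size Calculation section sizes the trial on one comparison: "To detect a difference in change between randomization and 12 weeks of 1500 steps per day (SD 2824"), with "n=74 participants per group [57 plus 17 for attrition"].

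The Statistical Methods section assigns models by type of outcome. Single continuous variables, with change in steps per day as the example, get a repeated-measures ANCOVA. For multiple continuous variables, with change in walking and MVPA as the example, "repeated measures multivariate analysis of covariance models will be used with the same covariates as the above model". It names no effect, visit or contrast that decides any hypothesis, and does not say whether steps are modelled at two or three time points. Table 2 shows steps measured at baseline, 5 weeks and 12 weeks. The section promises adjusted and unadjusted group means with 95% confidence intervals.

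**The concern.** A MANCOVA asks whether the groups differ on a vector of outcomes, in any direction. A significant result does not say which variable moved, which way, or over which interval. H3 to H6 ask exactly those things. The model that the article names for them is therefore the wrong kind of test, which goes beyond leaving a detail unstated.

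For steps the difficulty is narrower. A repeated-measures model over three time points offers several tests: a 2-df group-by-time test, a group effect averaged over visits, and single-visit contrasts. Only the 12-week contrast matches H1. The Primary Outcome section explains that 12 weeks was chosen to see whether steps persist after the 4-week intervention. An omnibus or averaged test could be significant because of the 5-week result alone, so an effect that had faded could be reported as primary success. With the term unnamed, it could also be chosen after the data are seen.

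**Working it through.** **Inputs from the Sample Size Calculation section:** difference 1500 steps per day, SD 2824, two-sided 5% level, 80% power, 57 evaluable per group, 23% attrition.

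**Assumptions (the article gives no figure):** the SD of change is 2824 at both visits; the correlation ρ between the 5-week and 12-week changes is 0.3 to 0.7; covariates are ignored; for energy expenditure, the correlation between walking and MVPA change is 0.3, also shown at 0 and 0.5.

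**1. Reproduce the plan's figure.** Standardized effect = 1500/2824 = 0.531. A two-sample t-test with 57 per group has noncentrality 0.531 × √(57/2) = 2.84 on 112 df, giving power 80.3%. Attrition: 57/0.77 = 74.03, stated as 74 per group, 148 in all. The figure reproduces, and it belongs to the single 12-week contrast.

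**2. Joint test of walking and MVPA.** For two standardized effects δ with correlation matrix R, Hotelling's test has noncentrality λ = (n/2) δ′R⁻¹δ, referred to F on 2 and 2n − 3 = 111 df. With δ = (+0.3, −0.3), λ = 28.5 × 2 × 0.09/(1 − ρ) = 5.13/(1 − ρ).

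| ρ | λ | Joint test rejects |
|---|---|---|
| 0 | 5.13 | 50% |
| 0.3 | 7.33 | 66% |
| 0.5 | 10.26 | 81% |

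A separate t-test of either variable rejects about 36% of the time. In this case one hypothesis is true and the other is reversed, and the joint result cannot show it.

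**3. Steps at two time points.** With baseline and 12 weeks only, the group-by-time F has 1 df and equals the squared t on change. A numerical check without covariates gave 7.285 for both. This fit tests H1 exactly.

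**4. Steps at three time points.** The 2-df test of the two changes uses the formula of step 2. The visit-averaged test compares the mean of the two changes, with SD 2824 × √((1 + ρ)/2).

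Effect of 1500 at 5 weeks and none at 12 weeks (H1 false): λ = 28.5 × 0.531²/(1 − ρ²) = 8.04/(1 − ρ²).

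| ρ | 2-df test | Visit-averaged test | 12-week contrast |
|---|---|---|---|
| 0.3 | 75% | 41% | 5% |
| 0.5 | 83% | 37% | 5% |
| 0.7 | 95% | 33% | 5% |

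Power under other patterns, over ρ = 0.3 to 0.7:

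| Effect at 5 / 12 weeks | 2-df test | Visit-averaged test | 12-week contrast |
|---|---|---|---|
| 750 / 1500 | 71% to 74% | 63% to 74% | 80% |
| 1500 / 1500 | 78% to 88% | 86% to 94% | 80% |

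The omnibus test is thus not always weaker. The consistent problem is that it answers another question.

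**The case against.** The strongest reply is that the article never says an omnibus test decides H1. It names the analysed variable as change in steps per day, defines the primary outcome as change to 12 weeks, and lists the 5-week change as a separate secondary outcome. One fit per listed outcome is a natural reading, and it tests H1 exactly. Even a three-time-point model can supply the 12-week contrast, and a statistical analysis plan that is not shown may name it. This stands: one cannot say that the plan fails to test H1, only that the article does not bind H1 to its contrast.

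For H3 to H6, the reply is that group means with confidence intervals are promised and that secondary results are meant to support the primary hypothesis rather than claim an effect. That lowers the stakes, but group means do not amount to a test of each hypothesis, and the stated model remains a joint one.

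Two stronger readings are tempting. The first is that the models run on complete cases and so contradict the stated "intention-to-treat principles, in which data at a given time point will not be excluded from the analysis". Deleting anyone with a missing visit belongs to the classical least-squares fit, and the article nowhere states it. It says that missing data will be handled by best practice under different scenarios, and that "The method of handling missing data will be reported in a future publication of the results". Imputation or a likelihood-based fit would satisfy all of this, so neither a contradiction nor a power loss from deleted patients is shown. The second is that the four quality-of-life scores enter one MANCOVA although "Items include reverse scores and overlap across dimensions". Quality of life is not named as a MANCOVA outcome, and with two assessments no omnibus test over several follow-up visits arises.

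**Conclusion.** The point holds in two parts of unequal strength. For H3 to H6, the named joint MANCOVA does not match four separate directional hypotheses. The 66% rejection rate with opposed effects illustrates this and rests on the assumed ±0.3 SD and correlation of 0.3. For H1, the deciding term is left open. The 75% to 95% (2-df) and 33% to 41% (visit-averaged) rejection rates apply only if steps are modelled at three time points, that test is the one read, and the assumed SDs and correlations hold; a two-time-point fit has no such problem. The sample size of 148 reproduces and is unaffected. The change should be made before the analysis, but it is no ground for doubting the design.

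**What to change.** In the Statistical Methods section:

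- Replace the MANCOVA with a separate model for each outcome. A likelihood-based mixed model for repeated measures adjusted for the baseline value is preferable, since it keeps participants with partial follow-up, in line with the intention-to-treat sentence.
- Name the between-group difference in change in steps per day at 12 weeks as the sole test of H1.
- Test H2 by the 5-week contrast for steps, and H3 to H6 each by the contrast for its own variable and visit.
- If the quality-of-life scores were to be modelled jointly, give each its own contrast as well.

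The wording should be fixed before group assignments are known to the analyst. No new data or participants are needed. The cost is slightly more analysis work and more separate secondary tests, which the article already says will carry no adjustment and will serve only to support the primary result.

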#### Outcomes of Theoretical Variables

Two outcomes assessed only at 5 weeks for Perceived autonomy support (PAS) were drawn from a French version of the Important Other Climate Questionnaire: (1) from a significant other (PAS-SO) and (2) from the intervention (PAS-WEB). These measures assess autonomy support felt from a significant other (PAS-SO) and from either research website visited (PAS-WEB). The two scores are the mean of responses of 6 items for each PAS (significant other [SO] vs intervention [WEB]) rated between “not at all true” (1) and “very true” (7). Higher scores represent greater levels of PAS. Reported Cronbach alphas across three assessments were between .86 and .89 [54].

Self-determined motivation is assessed at baseline and 5 weeks by the French version of the Treatment Self-Regulation Questionnaire. This measure assesses reasons to attain the recommendation of walking 150 minutes per week. We retained the 12 items that assess controlled motivation (6 items) and autonomous motivation (6 items). The two scores are the mean of responses of 6 items for each motivation (controlled vs autonomous) rated between “not at all true” (1) and “very true” (7). Higher scores represent greater levels of controlled and autonomous motivation. Reported Cronbach alphas across four populations were between .73 and .91 for controlled motivation, and between .85 and .93 for autonomous motivation [55].

Perceived competence is assessed at baseline and 5 weeks by the French version Perceived Competence Scale [53]. This measure assesses confidence to attain the recommendation of walking 150 minutes per week. The score is the mean of responses of 4 items rated between “not true at all” (1) and “very true” (7). Higher scores represent greater levels of perceived competence. Reported Cronbach alphas across two assessments were .93 and .96 [54].

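### The mediation analysis for H7 to H11 is planned as a sequence of one-way ANOVAs, which gives no indirect effect and so cannot show whether the constructs explain the effect on steps

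*Protocol article*

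**What the plan says.** Under Study Aim and Hypotheses, with 12 weeks as the time point for steps, the protocol article states the aim as "assessing if the change in SDT variables immediately postintervention at 5 weeks will explain the hypothesized increase in steps per day". It then says, for H7 to H11: "we will explore the mediating role of the SDT constructs (perceived autonomy support, controlled and autonomous motivations, perceived competence) and barrier self-efficacy".

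Statistical Methods gives one sentence on how this is done: "A mediation analysis will use a sequence of one-way analysis of variance models with Bonferroni adjustments". Under the Bonferroni rule stated there, alpha is split across the tests, but how many there are is not given. Nor are the factor and dependent variable of each model, or a rule for concluding that mediation is present.

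The same paragraph uses richer models elsewhere. For single continuous outcomes, "repeated measures analysis of covariance models will be used with covariates"; multivariate analysis of covariance and logistic regression are named for other outcome types.

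Under Outcomes of Theoretical Variables and in Table 2, controlled and autonomous motivation, perceived competence and barrier self-efficacy are measured at baseline and 5 weeks. Perceived autonomy support is different: "Two outcomes assessed only at 5 weeks for Perceived autonomy support (PAS"), as one score for a significant other (PAS-SO) and one for the website (PAS-WEB).

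**The concern.** A mediation claim has two links: the intervention moves the construct, and the construct moves steps. The second link has to be estimated with group held fixed, because randomization to the website can shift the construct and steps by separate routes. A one-way ANOVA has a single categorical factor. With group as that factor it shows the first link and the total effect on steps, and never the second link.

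This matters here because the intervention was built to move these constructs, as the Experimental Group section and Table 1 set out. A group difference in a construct is therefore expected by design, whether or not the construct affects walking. If such a difference, alongside a difference in steps, were read as mediation, the trial could report a theoretical mechanism that it had not tested. The article's Conclusion counts the examination of these processes among the study's strengths.

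**Working it through.** **1. What the models identify.** Let G be group, M the 5-week mediator and Y the change in steps, both in SD units:

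- M = aG + error
- Y = c′G + bM + error

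The ANOVA of M on group estimates a. The ANOVA of Y on group estimates c = c′ + ab. The indirect effect is ab, so b is needed, and these two comparisons do not fix it. Take a = 0.5 and c = 0.531. No mediation (b = 0, c′ = 0.531) and full mediation (b = 0.531/0.5 = 1.06, c′ = 0) give the same two group differences.

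**2. The plan's own figure.** Sample Size Calculation gives a difference of 1500 steps, SD 2824, two-sided 5%, 80% power and 23% attrition.

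- d = 1500/2824 = 0.531.
- Noncentral t: power 0.796 with 56 per arm and 0.803 with 57, so 57 per arm.
- 57/(1 − 0.23) = 74.03, stated as 74; 2 × 74 = 148. The figure is reproduced.

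The article gives no figure for the mediation analysis itself.

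**3. Illustration.** From the article: 57 per arm and d = 0.531 for steps. Assumed: b = 0 (M is not a mediator), normal data with unit variance, mediator shifts of 0.3, 0.5 and 0.8 SD, and a divisor of 5 (one per hypothesis). Each setting has 20,000 simulated trials. Entries are the share of trials in which a non-mediator is flagged.

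| Assumed rule | Alpha | 0.3 SD | 0.5 SD | 0.8 SD |
|---|---|---|---|---|
| Both group ANOVAs significant | 0.05 | 29% | 60% | 80% |
| Both group ANOVAs significant | 0.05/5 | 9% | 31% | 56% |
| Both group ANOVAs significant | 0.05/10 | 5% | 21% | 45% |
| As above, plus ANOVA of steps on median-split mediator | 0.05 | 2.6% | 6.1% | 12.0% |
| Group-to-mediator, and mediator-to-steps given group | 0.05 | 1.9% | 3.7% | 4.9% |
| Group-to-mediator, and mediator-to-steps given group | 0.05/5 | 0.2% | 0.6% | 0.9% |

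Check on the first two rows: with b = 0 the two tests are independent, so the rate is the product of their powers. At 0.05 the mediator test has power 0.360, 0.754 and 0.989; times 0.803 this gives 0.289, 0.605 and 0.794. At 0.05/5 it has 0.158, 0.522 and 0.949; times 0.586 this gives 0.093, 0.306 and 0.556. Both sets agree with the simulation.

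**4. Reading the table.** Bonferroni lowers the rates but does not cure the problem, because the ANOVAs test other null hypotheses. Making the categorized mediator the factor does not cure it either: group is then left out of that model and drives both variables, and the rate passes 5% at 0.5 SD and above. Conditioning on group keeps it at or below nominal.

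**The case against.** The strongest reply is that the illustration tests a rule the article never states. That stands. The article does not say that both group tests must be significant, does not give the steps in the sequence, and gives neither a mediator shift nor a divisor. A reader might infer that the plan would call any construct the website moves a mediator, or that its false-mediator rate is some particular figure. The text supports neither inference. The rates move widely with the assumptions, and a third ANOVA brings them down sharply.

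Other stronger readings also fail:

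- **Power.** A reader might say that Bonferroni cuts each step from 80% to 59% power. That borrows the steps effect for every mediator, and the mediator effects are unknown.
- **Baseline discarded.** The mediators and the primary outcome are framed as changes, and change scores use baseline. Covariate adjustment would be a matter of efficiency.
- **Change in autonomy support.** No change can be computed without a baseline, but PAS-WEB rates the website visited and can have no value before randomization. The 5-week score is the evident analysis variable, and the aim is loosely worded.
- **Contradiction on multiplicity.** No P-value adjustment is to be "made for the hypotheses on secondary and tertiary outcomes". The article classes the theoretical variables separately, so mediation can be read as its own adjusted family.

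It may also be said that a full protocol or analysis plan could describe regression steps. But the article names a technique, beside analysis of covariance for other outcomes, and one-way models as written exclude a joint model of group and mediator. This is a wrong stated method, not detail left to another document.

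**Conclusion.** The concern holds for the method as stated. A sequence of one-way ANOVAs yields no mediator-to-steps relation given group and no indirect effect, so it cannot answer H7 to H11. That conclusion follows from the structure of the models and needs no simulation.

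The size of the error is illustrative only. Under a both-tests-significant rule with assumed shifts of 0.3 to 0.8 SD, a non-mediator is flagged in about 29% to 80% of trials at 0.05 and 9% to 56% at 0.05/5. With an added median-split ANOVA the range is about 3% to 12% at 0.05. These are not properties of the trial.

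The point should be fixed, but it does not threaten the trial. A reader might infer that the main result is compromised; it is not. H7 to H11 are exploratory, and the primary hypothesis, its model and the sample size do not depend on this sentence.

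**What to change.** Replace the mediation sentence in Statistical Methods. For each mediator:

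1. Regress the 5-week mediator on group, its baseline value where measured, and the covariates already listed. The group coefficient is a.
2. Regress 12-week steps on group, the 5-week mediator, baseline steps, the baseline mediator where measured, and the same covariates. The mediator coefficient is b.
3. Report the indirect effect a × b with a bootstrap 95% confidence interval.

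State that PAS-WEB and PAS-SO enter as 5-week scores. State also that reading a × b causally assumes no unmeasured confounding of mediator and steps, since the mediator is not randomized. Whether to keep a Bonferroni adjustment for this family is optional; if it is kept, give the number of tests and say that mediation is a separately adjusted family.

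The cost is a change of wording and slightly more analysis work. Table 2 already schedules every variable needed, so no new data are required.
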